##### Attitudes toward digital health applications

Patients’ attitudes towards online interventions are measured as follows:g.Mean scores of the questionnaire “Attitudes toward Psychological Online Interventions–the APOI” ([APOI]; [57]).

### Participant timeline {13}

Smoking patients who have had three psychotherapeutic consultations at the Psychotherapeutic Outpatient Center of the University of Siegen will be informed about the option of participation in the current study. Interested participants will be contacted by the study team and undergo a telephone interview to determine eligibility and fulfillment of the inclusion criteria (*− t*_1_). Following telephone screening for a duration of 10–30 min, patients will be invited to the first smoking cessation session, during which informed consent will be obtained and psychological symptoms will be assessed within the course of a diagnostic session (baseline, *t*_*0*_). After the diagnostic session, during which all baseline measures will be assessed, patients will be randomly assigned either to the experimental group or the passive control group. The experimental condition will receive a 6-step smoking cessation program and additional access to a smartphone-based self-help application. The duration of the intervention will be three weeks. Afterwards, patients will be invited again to assess all measures of interest (*t*_1_). Six weeks (*t*_2_) and 6 months (*t*_3_) after completion, patients will be invited once again for follow-up assessments. The participants’ timelines and data assessment points are shown in Table 2..

**Table 2. Tab2:**
[figure not shown]
Participant timeline

### Sample size {14}

To estimate the required sample size, an a priori power analysis was conducted using G*Power 3.1.9.7 [21]. The primary hypothesis will be tested using a 2 × 4 mixed-design repeated-measures ANOVA (with a power of 1 − *β* = 0.80 and a significance level of *α* = 0.05. This requires a sample size of approximately 62 participants in total, 31 per condition, to detect a moderate effect. No additional participants will be recruited to compensate for potential dropout; instead, the study design follows the intention-to-treat (ITT) principle and employs multiple imputation methods to address missing data. The decision to target a moderate effect size is driven by practical considerations to detect treatment effects that are both statistically significant and practically meaningful.

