Additionally, personalized recommendations tailored to each individual’s smoking behavior will be provided. Detailed descriptions of the individual sessions are outlined in the manual by Batra and Buchkremer [4]. In this research project, we will augment the original program by increasing session frequency and incorporating a self-help smoking cessation smartphone application to address specific challenges faced by smokers with mental disorders. While the original program was designed with weekly sessions over a course of 6 weeks, our intensified version will include two sessions per week, shortening the intervention duration to three weeks. Furthermore, participants will have access to the digital health application (*NichtraucherHelden®*,Sanero Medical GmbH, Stuttgart, Germany), a CBT-based self-help app featuring eight modules of psychoeducation, tasks, and relapse prevention. Recent evidence from a nationwide, multicentric, parallel, randomized controlled trial demonstrated the app’s feasibility and efficacy, with the intervention condition showing twice the abstinence rates at a 7-day point prevalence compared to the control condition [54].

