## Statistical methods

### Statistical methods for primary and secondary outcomes {20a}

Treatment effects on the continuous primary outcomes (i.e., tobacco dependence, smoking intensity, mental health symptoms) will be tested by computing mixed 2 (condition) × 4 (time) analyses of variance (ANOVAs) for repeated measurements for each applied outcome variable. To reduce the likelihood of Type I errors due to multiple comparisons, the false discovery rate (FDR) will be controlled using the Benjamini-Hochberg procedure [7] across the primary outcome measures. In the case of potential violations of the sphericity assumption, the Greenhouse–Geisser method will be applied.

It will be examined whether the experimental condition leads to higher abstinence rates at post- and follow-up assessments using chi-squared tests.

Secondary and exploratory analyses testing for potential mediating variables will be conducted using regression analyses or structural equation modeling. Treatment effects on the AAT will be tested by computing mixed 2 (condition) × 4 (picture category) analyses of variance.

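### The stated 80% power at N = 62 applies to one ANOVA at unadjusted alpha 0.05 with complete data, not to about eight primary outcomes under Benjamini-Hochberg with no dropout allowance

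*Protocol article*

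**What the plan says.** Protocol article, Sample size {14}, frames the calculation around one test: "The primary hypothesis will be tested using a 2 × 4 mixed-design repeated-measures ANOVA". The target is 80% power, and the alpha is an unadjusted 5%. The result is given as: "This requires a sample size of approximately 62 participants in total, 31 per condition, to detect a moderate effect". No number is attached to the effect. On attrition the section adds: "No additional participants will be recruited to compensate for potential dropout; instead, the study design follows the intention-to-treat (ITT) principle", with multiple imputation named as the means of handling missing data.

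Outcomes {12} lists eight primary measures. Four concern smoking (FTND, ASSIST tobacco subscale, exhaled CO, and urine cotinine as positive/negative). Four concern mental health (WHO-5, WHOQOL-BREF, BSCL, BDI-II).

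Statistical methods {20a} gives each continuous outcome its own 2 × 4 ANOVA, compares abstinence by chi-squared tests at post-treatment and follow-up, and states that "the false discovery rate (FDR) will be controlled using the Benjamini-Hochberg procedure [7] across the primary outcome measures". Greenhouse-Geisser is used if sphericity is in doubt. The section on missing data {20c} specifies chained-equation imputation under missing at random.

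**The concern.** The power statement and the decision rule describe different trials. Power is quoted for one hypothesis at 0.05. The analysis applies a multiplicity procedure whose thresholds cannot exceed its nominal level and are mostly below it. No section carries this adjustment, or any dropout rate, into the sample size.

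The reasoning on dropout is also faulty. Under missing at random, imputation guards against bias and uses the visits that were observed. It cannot supply more information than complete data would, and 62 is already the complete-data requirement.

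What is at stake is how null results are read. A non-significant outcome would be taken as coming from an 80%-powered test when, under the plan's own rule, it does not. The binary smoking-status outcome has no power statement at all.

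**Working it through.** **Inputs from the protocol.** N = 62, 31 per arm; 2 groups, 4 times; alpha 0.05; power 0.80; a moderate effect, unquantified; eight primary measures; Benjamini-Hochberg; no dropout inflation.

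**Inputs assumed.** f = 0.25 for a moderate effect unless stated; q = 0.05; dropout 10–30%; within-person correlation ρ = 0.5 where needed.

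**Step 1: reproduce 62.** Noncentral F for the group × time interaction with sphericity (ε = 1), degrees of freedom 3 and 3(N − 2) = 180:

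- Partial-eta-squared scaling: λ = f²(N − 2)(4 − 1) = 0.0625 × 60 × 3 = 11.25, power 0.804. At N = 60 power is 0.789, so 62 is the smallest even N.
- G*Power default scaling with f = 0.15, ρ = 0.5: λ = f²·N·4/(1 − ρ) = 0.0225 × 62 × 4/0.5 = 11.16, power 0.801.
- Between-groups effect with f = 0.25, ρ = 0.3: λ = 0.0625 × 62 × 4/(1 + 3 × 0.3) = 8.16, F(1, 60), power 0.802.
- By contrast, the default scaling with f = 0.25, ρ = 0.5 needs only 24.

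So 62 is reproducible, but by more than one route. The article does not show which was used.

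**Step 2: Benjamini-Hochberg, complete data.** With m = 8 and q = 0.05, the threshold runs from 0.05/8 = 0.00625 at the strictest step to 0.05 at the loosest. With λ = 11.25, power at 0.00625 is 0.532. If the family has seven tests, the strictest step is 0.05/7 = 0.00714 and power is 0.549. Simulations of eight tests, using the two interaction scalings above that give 62, yield this average power per truly affected outcome:

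| Truly affected outcomes | Independent | Correlated at 0.5 |
|---|---|---|
| 1 of 8 | 0.53–0.54 | 0.53 |
| 2 of 8 | 0.59–0.60 | 0.59 |
| 4 of 8 | 0.67–0.68 | 0.66 |
| 8 of 8 | 0.77–0.78 | 0.74 |

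**Step 3: dropout alone, one ANOVA at alpha 0.05.** On completers:

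| Assumed loss | Retained N | Power |
|---|---|---|
| 10% | 56 | 0.75–0.76 |
| 20% | 50 | 0.70 |
| 30% | 44 | 0.63 |

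If imputation recovers everything contained in the visits that dropouts did attend, power at 20% loss lies between about 0.74 (all leave before post-treatment) and 0.79 (all miss only the last visit). This takes ρ = 0.5 and an effect sustained over the three later visits. Even the best case stays below the complete-data value.

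**Step 4: both together.** At 20% loss on completers with Benjamini-Hochberg, power per affected outcome is about 0.40–0.41 (one affected) to 0.61–0.64 (all eight). This is a pessimistic bound, because the planned analysis imputes.

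**Step 5: sphericity.** If ε were 0.75 (an assumption; the protocol gives no value), a Greenhouse-Geisser-corrected test would have power of about 0.71 with complete data.

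**Step 6: binary outcome.** The ANOVA calculation says nothing about a chi-squared comparison of 31 against 31. As an illustration of how far the conditions matter, 10% versus 40% abstinence has power 0.81 at alpha 0.05 with 31 per arm, 0.52 at alpha 0.00625, and 0.73 at alpha 0.05 with 25 per arm.

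**The case against.** The strongest reply is that nothing has been miscalculated. The figure of 62 reproduces, and the section openly states one ANOVA, alpha 0.05 and no allowance. That stands: the fault lies in what the 80% is taken to cover, not in the arithmetic.

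A second reply is that Objectives {7} expects benefit on nearly all outcomes. If all eight respond, Benjamini-Hochberg alone costs only about 3 to 6 points, and the chance of finding at least one effect is above 90%. This also stands. A reader might infer from the one-in-eight row that the trial's real power is 53%, but no section proposes that only one outcome will respond. Equally, the protocol does not define success as finding at least one effect, so that figure does not rescue the 80%.

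Other stronger readings are also unsupported:

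- **The 40–64% range as the trial's power.** It rests on an assumed 20% loss and a completers-only analysis.
- **A fixed threshold of 0.00625.** Neither q nor the exact family is stated. The family could be the seven ANOVAs, eight measures, or more if each chi-squared time point counts, and one heading also labels the approach-bias task as primary. Seven tests instead of eight changes little.
- **Routine Greenhouse-Geisser loss.** The correction is conditional.
- **A specific effect implied by 62.** Several scalings give 62, so a translation into a standardised difference is not a property of the plan.
- **Low power for a doubling of abstinence.** Intervention description {11a} cites an app trial "showing twice the abstinence rates at a 7-day point prevalence compared to the control condition", but that concerns the app without the six sessions and a different abstinence measure. The protocol adopts neither a doubling nor a control rate.

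Finally, the numeric effect size may be in the full protocol. That is fair, so its absence from the article is not the finding itself. It does mean that 62 cannot be tied to one target effect from the article.

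**Conclusion.** The point holds in limited form and should be fixed. The 80% is correct for one 2 × 4 ANOVA at unadjusted alpha 0.05 with complete data and sphericity. It is not the power of the analysis described in Statistical methods {20a}.

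The shortfall from multiplicity alone ranges from a few points (all eight outcomes respond) to about 27 points (one responds), taking eight tests and q = 0.05. Dropout of 20%, if it occurred, would cost a single ANOVA roughly 1 to 10 points, depending on when patients leave and how much imputation recovers. The direction needs none of these assumed values: since 62 has no reserve, any loss of information, or any threshold below 0.05, takes power under 80%. The statement that imputation is used in place of an allowance is wrong as reasoning, whatever the dropout rate.

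**What to change.** Revise Sample size {14}; no patients need to be added.

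1. Give the numeric effect size, the assumed correlation and the G*Power effect-size option that led to 62.
2. Say that 80% refers to one ANOVA at unadjusted alpha 0.05 with complete data and sphericity.
3. Add power per outcome under Benjamini-Hochberg, at the expected dropout, for a stated number of truly affected outcomes. Name the family of tests and q. If a non-sphericity value such as ε = 0.75 is used, label it as an assumption.
4. Give the abstinence difference that the chi-squared test can detect at the same adjusted threshold and retained N. An unadjusted complete-data example such as 10% versus 40% would repeat the fault.
5. Remove the word that makes imputation a substitute for a dropout allowance. Keep imputation as the missing-data method, and state separately that no allowance is made and what that costs in power.

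The cost is a change of wording, a short recalculation and a less favourable stated power. The analysis itself does not change.

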### Recruitment {15}

Participants will be recruited among individuals identified as regular smokers who previously had up to three psychotherapeutic consultations in the outpatient psychotherapeutic clinic at the University of Siegen. If the inclusion rate does not meet the requirements, additional advertisements to enhance participation in this project will be installed by the research team. If necessary, the planned duration of the enrollment period of 1 year will be extended.

## Assignment of interventions: allocation

### Sequence generation {16a}

Participants will undergo random allocation to either the experimental or control condition at a 1:1 ratio. Given the study design, participant or therapist blinding post-allocation is not feasible.

### Concealment mechanism {16b}

No concealment mechanism, the groups are randomly allocated.

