### Eligibility criteria {10}

Participants must be at least 18 years old and exhibit harmful use of tobacco (F17.1 according to the ICD-10; [47]) or tobacco dependence (F17.2 according to the ICD-10) while also fulfilling the criteria for a treatment-relevant primary mental disorder. An exclusion criterion is acute suicidality, as well as the presence of an acute psychotic episode or the use of certain medications (e.g., neuroleptics such as Clozapine), where unmonitored cessation without a psychiatrist’s oversight may pose significant risks. The smoking intervention will be performed by trained clinical psychologists, while all psychotherapeutic consultations will be performed by trained psychological psychotherapists. If additional substance use disorders are present, treatment of these disorders is prioritized in accordance with German clinical guidelines [62] and ethical standards, particularly when inpatient treatment is indicated. Smoking cessation is then offered as an adjunctive treatment once the primary substance-related condition is overcome. This approach ensures appropriate care and participant safety.

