### Who will take informed consent? {26a}

The informed consent of study participants is ensured through a comprehensive briefing at the initiation of the study (initial session) by the clinical psychologist. After receiving and reviewing the information, participants’ consent will be obtained.

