### Implementation {16c}

A research assistant or psychotherapist will communicate the allocation to patients and introduce them to either the intervention or the control condition.

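### The protocol disclaims allocation concealment on the ground that groups are randomised; randomisation does not supply it, so the open-label trial is exposed to selection before assignment

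*Protocol article*

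**What the plan says.** All statements are in the protocol article.

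- Concealment mechanism {16b}: "No concealment mechanism, the groups are randomly allocated". That is the whole entry.
- Sequence generation {16a}: "Participants will undergo random allocation to either the experimental or control condition at a 1:1 ratio". Of the period afterwards it says that "participant or therapist blinding post-allocation is not feasible". Who will be blinded {17a} confirms that nobody is blinded.
- Implementation {16c}: "A research assistant or psychotherapist will communicate the allocation to patients".
- Participant timeline {13}, on screening: "Interested participants will be contacted by the study team and undergo a telephone interview to determine eligibility". On the order of events: "After the diagnostic session, during which all baseline measures will be assessed, patients will be randomly assigned either to the experimental group".
- Who will take informed consent? {26a}: consent follows a "comprehensive briefing at the initiation of the study (initial session) by the clinical psychologist".
- Eligibility criteria {10}: "The smoking intervention will be performed by trained clinical psychologists".

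The section on the coordinating centre {5d} adds that psychotherapists raise study participation with patients during routine care. It also describes a stakeholder group of ten psychotherapists who do not deliver the cessation programme. No section mentions a central or web service, envelopes, or an independent holder of the sequence.

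**The concern.** Random generation makes the order of assignments a matter of chance. Concealment keeps the next assignment from those who decide who enters, and when, until the patient is irrevocably in the trial. A random list that recruiting staff can read gives the first property without the second. The entry under {16b} treats the first as if it made the second unnecessary.

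This is more than detail lost in condensing a protocol into an article. The item is answered: the safeguard is declared absent and a reason is given.

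The setting supplies both motive and opportunity. Controls wait six months for the programme (Trial design {8}), so staff may want a particular patient treated now. The Discussion says that entry is not restricted by willingness to quit, so candidates will differ in motivation. If such differences influence who enters when a given arm is next, the arms differ in prognosis before treatment begins. Analysis can repair that only in part, because adjustment reaches only what was measured.

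**Working it through.** **Step 1: does any section supply what {16b} disclaims?** Following a patient through the plan:

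| Step | Who | Section |
|---|---|---|
| Raising participation | psychotherapists | {5d} |
| Telephone screening | study team | {13} |
| Consent | clinical psychologist | {26a} |
| Allocation | not stated | {13}, {16a} |
| Conveying the arm | research assistant or psychotherapist | {16c} |
| Delivering the programme | clinical psychologists | {10} |

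The allocation row names no generator, holder or release procedure. Nothing separates the sequence from the people in the other rows.

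**Step 2: does infeasible blinding explain the gap?** No. The statement in {16a} concerns the time after allocation. Concealment ends when the arm is disclosed, so a trial in which everyone later knows the treatment can still conceal.

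**Step 3: what does the planned order protect?** Allocation follows consent and all baseline measures. The baseline scores therefore cannot be coloured by knowledge of the arm, and there is little room to drop a patient between baseline and allocation. Screening, encouragement to consent and scheduling all come earlier. If the next assignment is visible or predictable, those steps remain open.

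**Step 4: size, by illustration only.** The arm size is 62/2 = 31 (Sample size {14}). The number of patients affected, k, and the 1 SD gap in prognosis for the outcome are assumptions; the protocol gives neither. If k poor-prognosis patients in one arm change places with k good-prognosis patients in the other, one arm mean rises by k/31 SD and the other falls by k/31 SD:

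shift = 2k/31 SD

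- k = 1: 2/31 = 0.065 SD
- k = 2: 4/31 = 0.13 SD
- k = 3: 6/31 = 0.19 SD

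For scale, take a plain two-group comparison at two-sided 0.05 with 31 per arm. The standard error is √(2/31) = 0.254 SD. A spurious shift of 0.2 SD then raises the type I error from 5% to about 12.3%. This is not the planned analysis, which is a condition-by-time ANOVA. The figure only shows that a handful of patients can matter at this sample size.

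Concealment does not alter the required sample size, so the planned 62 is not at issue here.

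**The case against.** The strongest reply is that the route to bias is conditional. The protocol mentions neither a list nor blocks. If each patient is assigned by a simple draw made after baseline, there is no next assignment to foresee. That is fair, and it is why the size of the exposure cannot be stated. It does not rescue the entry, because the protocol describes no such draw and gives randomisation itself as the reason for having no mechanism.

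Second, the arithmetic moves an arm's level, whereas the planned test is of condition by time. A severity difference that stays constant over time creates no interaction. This stands: the shift applies only so far as the swapped patients differ in how they would change. Motivation could plausibly act in that way; stable severity may not.

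Third, motivation and symptoms are measured at baseline, so imbalance in them would be visible, and {20b} allows re-analysis for confounding. That helps, but the re-analysis is discretionary and cannot reach unmeasured differences.

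A reader might also infer more than the documents support:

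- **That one small team does everything.** The sections name different roles, and {10} distinguishes the psychologists who treat from the psychotherapists who consult. Overlap is possible but not stated. What can be said is that no independent holder is named.
- **That the trial targets an effect of about 0.7 SD, against which the shift can be judged.** {14} says only that the effect is moderate, for a 2 × 4 mixed ANOVA. A value of 0.72 SD is what 31 per arm detects with 80% power in a plain two-group comparison, which is a different test.
- **That self-reported outcomes aggravate this problem.** They raise a separate issue, response bias after allocation.
- **That selection has taken place.** Nothing in the protocol shows it.

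**Conclusion.** The point holds as a matter of exposure. The protocol expressly declares that there is no concealment, gives a reason that does not follow, and has no other provision that fills the gap. Randomising after consent and baseline reduces the exposure but leaves screening, consent and scheduling open if assignments can be seen or predicted.

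The size is unknown. The shifts of 0.13 and 0.19 SD rest on an assumed two or three swaps per arm of 31, a gap of 1 SD, and prognosis that bears on the outcome as analysed. The conclusion does not depend on those figures. It rests on the text of {16b} and on the absence of a named independent holder. It should be put right because a basic safeguard of randomisation is disclaimed, later analysis cannot fully restore it, and providing it costs little.

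**What to change.** For all remaining participants, replace the entry under {16b} with a procedure along these lines:

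- A computer-generated 1:1 sequence with randomly varied block sizes, so that unblinded staff cannot deduce the next arm from earlier ones.
- The sequence is made and held by an existing university member who does not refer, screen, take consent, treat or announce arms. The stakeholder group is not a safe choice: its members are psychotherapists, and psychotherapists raise participation with patients ({5d}) and may convey the arm ({16c}).
- Each assignment is released from a locked server file or a sealed opaque envelope, with date and time logged, only after consent and all baseline measures are recorded. This keeps the order already set in {13}.
- The trial report states how many patients were randomised before the change.

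Data collection began in August 2024 (Trial status), with enrolment planned for one year and extendable ({15}), so recruitment may already be over. If so, the sponsor should state how assignments were actually generated and released, withdraw randomisation as the reason for having no concealment, and report any lack of concealment as a limitation.

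The cost is a short amendment by the route in {25}, some time from one existing person, and a small delay at each randomisation. No new staff are needed.
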